## Abstract

**Background:**

The overall number of cancer cases is increasing and, therefore, strengthening cancer prevention has become a priority. The institutions responsible for its control establish guidelines for primary prevention. These include recommendations, such as: not smoking, following a healthy diet, doing daily physical exercise or avoiding overweight. Adolescence is a period of adoption and/or consolidation of health behaviors, and both school- and family-based interventions have proven effective to improve them. Furthermore, online and mobile phone educational interventions are encouraging. Consequently, the main aim of this study is to assess the efficacy of an intervention in which these requirements (school, family, the Internet and SMS) are combined to prevent behavioral cancer risk.

**Methods:**

This protocol describes the design and implementation of a complex online program that includes a randomized controlled trial put into practice in two countries: Spain and Mexico. Adolescents and adults of their environment (relatives and teachers) who voluntarily participate will be randomly assigned to the experimental group or to the control group once they have completed the online pre-test. The experimental group members will have free access to a tailor-made and interactive website (http://www.alertagrumete.com). During the academic year, this website will be periodically updated with different school and leisure activities related to the avoidance of risk behaviors. To encourage participation, the program includes a competition that gives rewards to the winners. SMS are also sent to students to stimulate the adoption of healthy behaviors and as a reminder of participation. Finished the intervention, an online post-test is performed in both groups and the impact on the risk behaviors is therefore assessed.

**Discussion:**

The program is pioneer, since it combines many components which have already proven effective in previous researches. Moreover, it aims to compare efficacy in two countries with different socio-economic levels to find out if these approaches are equally effective in countries with a lower income level. However, the vertiginous evolution of the Internet and mobile phones may make this tool less attractive for adolescents, who may prefer social networks and other mobile phone applications which are nowadays massively used by their peers.

**Trial registration:**

ISRCTN27988779

## Background

### The current situation of cancer

In spite of the numerous implemented strategies for cancer control, it has not yet been possible to slow down the increasing number of diagnosis of this disease around the world. According to different estimates, in the less economically developed countries the incidence of cancer cases will be multiplied during the next decades; even in the richest countries, an immediate decrease is not expected [1]. If we also bear in mind the significant consequences (both mortal and non-mortal) that frequently take place after cancer is diagnosed, we could conclude that it is the disease which people and governments are most worried about [2]. Consequently, the percentage of the total health expenditure which is invested in cancer has increased in all countries, and it could even be unsustainable in the near future. For this reason, nowadays prestigious institutions are demanding an urgent improvement and the implementation of prevention strategies [3].

Although the main reason that underlies the relative failure in cancer control is the aging of the population, the external risk factors are the ones that lead to accumulative damages in the genome, and which end up causing the disease [4]. Therefore, we consider it is essential to suppress all the modifiable risk factors that are basically associated to health-related behaviors. According to the most current estimates, around 50% of the cancer cases per year could be avoided if the main triggering behaviors were suppressed [5-7].

### Guides for prevention

Different institutions of virtually all regions of the world establish and periodically broadcast advice about cancer prevention [8,9]. These recommendations seem to be effective in the reduction of (a) the global risk for cancer – as stated by the EPIC study [10], which is based in the assessment of more than 386,355 participants in nine European countries – and of (b) other chronic diseases of high prevalence [11]. One of the easiest and most complete guides is the “European Code Against Cancer” (ECAC) [12], which points out that “many aspects of general health can be improved and many cancer deaths prevented, if we adopt healthier lifestyles” (Table 1). The fourth revision of this guide is currently under elaboration.

**Table 1 T1:** **European Code Against Cancer** (**third version**): **primary prevention advice**

**Risk behaviors**	**Advices**
Smoking	1. Do not smoke; if you smoke, stop doing so. If you fail to stop, do not smoke in the presence of non-smokers.
Overweight	2. Avoid obesity.
Sedentary	3. Undertake some brisk, physical activity every day.
Unhealthy diet	4. Increase your daily intake and variety of vegetables and fruits: eat at least five servings daily. Limit your intake of foods containing fats from animal sources.
Alcohol consumption	5. If you drink alcohol, whether beer, wine or spirits, moderate your consumption to two drinks per day if you are a man or one drink per day if you are a woman.
Ultraviolet radiation exposure	6. Care must be taken to avoid excessive sun exposure. It is specifically important to protect children and adolescents. For individuals who have a tendency to burn in the sun, active protective measures must be taken throughout life.
Workplace exposure to carcinogens	7. Apply strictly regulations aimed at preventing any exposure to known cancer-causing substances. Follow all health and safety instructions on substances which may cause cancer. Follow advice of national radiation protection offices.

### The current situation of primary prevention of cancer

During the last years, different intervention programs have been created with the aim of modifying, individually or collectively, the risk behaviors that refer to the above mentioned code. Some of them have had great success and others less, but what is sure is that all of them have contributed to identify those aspects that could increase the efficacy of this kind of programs. In these studies, we can observe that all experts agree on highlighting the importance of acting first and foremost on groups with a high risk. We consider the membership in these groups should preferably be based on socioeconomic or behavioral criteria [13], since the selection according to genetic predisposition could cause inequalities because the use of this resource is not generalized [14]. In addition we should bear in mind that children and adolescents are a particularly vulnerable group, as it is at this crucial stage when the main cancer risk behaviors start and are consolidated. Furthermore, scientific literature also warns that the preventive interventions should not be dissociated from the environment in which these behaviors are usually acquired (in the case of adolescents, school and family environment) [15,16]. In this respect, the Internet is a tool that could act as a link with the environments that are frequently visited by young people and, in addition, it perfectly adapts to their linguistic and behavioral codes. Related to this idea, Albreht et al. [17] point out that in order to face the challenges that an integral fight against cancer involves, research should be focused on those interventions that bring us closer to the social marketing. In the case of adolescents, it inevitably leads to the Internet. There are different examples of web-based interventions which are able to modify risk behaviors [18-21], and there are even some manuscripts which describe protocols of similar studies [22-24]. However, since this is a very recent approach, there is not yet an absolute consensus about its utility [25], and therefore further research in this field is still needed.

In addition, it is also well-known that multiple interventions are increasingly necessary, and that is because (a) individuals usually have more than only one risk behavior, and mainly since (b) this kind of interventions require fewer resources.

To conclude, we would like to highlight that the most promising strategies should be based on others that have proven effective, and above all, on psychosocial theories, which are the ones that best explain the behaviors we wish to prevent [26].

### Aim

This article describes the design of a program called “Prevencanadol” (acronym for the words Prevention/Cancer/Adolescents). Its main aim is to assess the impact of an educational intervention managed via the Internet and mobile phones in order to prevent the behavioral cancer risk among adolescents and their adult environment (family and school). Its secondary aims are: (a) to evaluate the feasibility of the program and (b) to identify the educational needs of focal groups and their priority.

## Methods and design

### Type of study

A randomized controlled trial (using pre- and post-intervention assessments) has been designed in order to determine the impact that this web- and SMS-based intervention has on the Spanish and Mexican population between 12 and 16 years old and their adult environment regarding the following of the ECAC primary prevention advice. The design also includes a study of feasibility (i.e., assessment of the implementation procedure), as well as a descriptive study of the risk behaviors showed by the participants of the pre-test, in order to identify those individuals with the highest behavioral cancer risk.

### Study population and composition of the groups

The study population is composed of Spanish and Mexican students of Secondary Education, aged between 12 and 16, who have voluntarily accepted to participate in an educational program which is managed online and supplemented with the delivery of SMS. Due to the program characteristics, it is required to have access to the Internet at home or at school. However, mobile phones are optional. Adults of the environment of the student (family or teachers) can also participate in the program: (a) they can be previously invited by an adolescent or (b) they can also join spontaneously.

Students and adults should register onto the Prevencanadol website. Then, a computerized and randomized process will distribute them in an experimental group (EG) and in a control group (CG). According to the program characteristics, the randomization is subject to these two requirements: (a) 60% of the users should be assigned to the CG since a higher withdrawal rate is expected in this group; and (b) members of the same classroom or family should share a study group so as to avoid the possible contamination of the groups.

In order to detect a significant decrease (p<0.05) of at least 10 percentage points in the global behavioral risk indicator during the post-test, it will be necessary to recruit 622 individuals in each arm of the study (statistical power = 90% and estimated withdrawals = 20%).

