The obtained information allows us to design the ‛*main result variable*’, which is a synthetic indicator of the percentage of cancer risk in each individual based on his/her risk behaviors (i.e., the so called ‛global cancer behavioral risk’). This indicator is calculated by simply adding up all the risk points obtained by each person when he/she did follow the ECAC advice (Table 2); that means that a scoring of 100 shows the maximal behavioral cancer risk. These risk points are obtained from the percentage of responsibility for cancer, and according to scientific evidence, every behavior of the participant is responsible for this percentage [5-7,30,31]. To know if the individuals are following or not the advice, we will (a) apply the stages of change pointed out by Prochaska and DiClemente to each behavior and we will (b) use a questionnaire of frequency of food intake (regarding both risk foods and cancer protective foods). This questionnaire also includes information related to many variables, which according to scientific literature could modify the effect, since they influence the following (or lack of following) of the ECAC advice. These variables are: (a) *socio*-*demographic variables* (e.g., age, gender, country of residence – Spain or Mexico –, cohabitation, number of siblings, academic level, academic level of parents, weekly expenses, among others), (b) *family history of cancer* and (c) *determining factors of the A*.*S*.*E*. *Model* (i.e., social influence and self-efficacy for each behavior). Other variables which are related to the educational intervention are also controlled (e.g., SMS delivery, score obtained in the competition, number of months that the student is registered in the website, etc.).

**Table 2 T2:** **How to calculate the indicator**: “**total cancer behavioral risk**” (**principal result variable**)

**Cancer behavioral risk**	**Points**
Smoking	35
Not eating five servings of fruit and vegetables per day	20
Eating three or more daily fatty foods	10
Quotient “frequency of protection food/risk food” ≤0.9	8
Obesity/Overweight	15/10
Excessive drinking	5
Sedentary	5
Ultraviolet radiation exposure without protection	2
Workplace exposure to carcinogens*	5
Maximum punctuation in adolescents	100^†^

*Only in adults. ^†^ 105 points in adults.

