## Discussion

In this section we aim to discuss the main features of the methodological design of Prevencanadol:

Firstly, the project complies with the basic requirements for a parallel randomized controlled trial: (a) the study factor is artificially manipulated (online educational intervention and delivery of SMS) and (b) the study population is randomly distributed to an EG and to a CG. Notwithstanding that, this randomization is determined by the first registered student of a classroom, and consequently real classroom randomization is achieved. From this standpoint, this trial can be considered a cluster randomized controlled trial, which is a very useful design to avoid the possible contamination of the groups. However, an important limitation of the experimentation with educational interventions is that it is not possible to guarantee that participants have received the content of the intervention, as it could be done if it were a pill, for instance. But Prevencanadol has managed to reduce this limitation since it has incorporated in the statistical analysis the scoring obtained during the competition, which is an indirect indicator of the reception degree of the intervention.

Secondly, as already pointed out, the program addresses a target population between 12 and 16 years old in order to reach the highest cancer preventive efficacy, since adolescence is a vital stage in which many behaviors (that will shape the adult stage) are acquired and consolidated. Although it can be a difficult age range, prevention of risk behaviors in this population group is also possible, especially if advice is linked to the school context [32-34]. However, it is not a task that is exclusively linked to school: we should bear in mind that society and family can be important sources of behaviors [35], and therefore we also encourage the registering of adults (teachers and family) in the website http://www.alertagrumete.com. In this way, it is even possible that healthy adolescents also become instigators of some preventive behaviors among adults; that consequently achieves ascending education. Finally, regarding the diversity of participants, we should also mention that we could only have included in the program adolescents with established risk behaviors, as other authors do in their works [36], but in our opinion when working with such a young population, it is as necessary to treat existing risk behaviors as well as to prevent their presence.

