To sum up, Prevencanadol could be considered groundbreaking, since it (a) aims to link family and school environments, (b) combines the use of the Internet and the delivery of SMS, (c) considers psychosocial models which are supported internationally, (d) intervenes in six behaviors simultaneously, and (e) compares the efficacy of the intervention in a country with a high income level (Spain) with that obtained in another one with a middle income level (Mexico).

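### Allocation is not stratified by country; if Mexico supplies few classrooms, a chance imbalance there would modestly weaken the advertised Spain–Mexico comparison

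*Protocol article*

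**What the plan says.** In the section on study population and group composition, the protocol article states that "the randomization is subject to these two requirements". The first is that "60% of the users should be assigned to the CG since a higher withdrawal rate is expected in this group". The second is that "members of the same classroom or family should share a study group so as to avoid the possible contamination of the groups". No other constraint is given.

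The Discussion adds that "this randomization is determined by the first registered student of a classroom", and that "consequently real classroom randomization is achieved". The units that receive an arm are therefore mainly classrooms, taken one at a time as their first student registers.

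On country, the Discussion part of the Abstract says of the program that "it aims to compare efficacy in two countries with different socio-economic levels", and the closing paragraph of the main Discussion repeats this as one of the study's distinguishing features. The section on assessing impact lists "country of residence – Spain or Mexico" among the variables that could modify the effect, and the regression is to control for confounders and effect modifiers. The Aim section does not name a country comparison as a main or secondary aim.

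**The concern.** When whole classrooms are allocated, the number of random units in one country can be small even if the trial has many participants. With no constraint by country, the 60:40 ratio can hold overall while one country departs from it by chance.

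The stake is precision, not bias. Country can be adjusted for in the regression, and that removes confounding of the overall effect by country. It cannot restore information on the Mexican effect if very few Mexican classrooms fall in one arm. The comparison between countries is built on that effect. If the variance per classroom is the same in both countries and Mexico supplies a fraction f of the classrooms, Mexico contributes a fraction 1 − f of the variance of the contrast. At f = 20–30% that is 70–80%, so most of any Mexican loss carries through.

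**Working it through.** **The plan's own figure.** The only sample size given is 622 per arm for the whole trial, with no figure by country. It cannot be derived from the article alone, because no baseline rate or standard deviation is stated. Assumed inputs come close: 50% against 40%, two-sided, gives 519, and 519 × 1.2 = 623; 40% against 30% with continuity correction gives 496, and 496 / 0.8 = 620. The figure is not in dispute here.

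**Inputs**
- Experimental-group (EG) target share: 40% (from the 60% control rule).
- Unit: classroom (Discussion).
- Number of Mexican classrooms, m: not stated. Assumption: 50–80 participating classrooms, 20–30% of them Mexican. This gives 50 × 0.2 = 10, 50 × 0.3 = 15, 80 × 0.2 = 16 and 80 × 0.3 = 24.
- If half the classrooms are Mexican: m = 25 to 40.
- Further assumptions: equal classroom sizes and independent allocation of each classroom.

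**Formulas.** The number of Mexican classrooms in EG is Binomial(m, 0.4). With EG share q, the variance of the within-Mexico effect relative to a fixed 60:40 split is 0.24 / [q(1 − q)]. This equals 1 at q = 0.4 and at q = 0.6, and is below 1 between them.

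**Worked case, m = 10**

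| EG classrooms | Probability | Relative variance |
|---|---|---|
| 1 or 9 | 0.0403 + 0.0016 | 2.667 |
| 2 or 8 | 0.1209 + 0.0106 | 1.500 |
| 3 or 7 | 0.2150 + 0.0425 | 1.143 |
| 4 or 6 | 0.2508 + 0.1115 | 1.000 |
| 5 | 0.2007 | 0.960 |
| 0 or 10 | 0.006 | effect not estimable |

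Averaged over the estimable splits: (0.0419 × 2.667 + 0.1315 × 1.5 + 0.2575 × 1.143 + 0.3623 × 1 + 0.2007 × 0.96) / 0.994 = 1.165, an increase of 16.5%. In interval width, √1.165 = 1.08, about 8%.

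**All cases**

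| m | Average variance increase | Chance of more than 20% increase | Chance of no loss | Chance EG share under 25% | Chance EG share over 60% |
|---|---|---|---|---|---|
| 10 | 16.5% | 18% | 56% | 16.7% | 5.5% |
| 15 | 10.7% | 23% | 56% | 9.1% | 3.4% |
| 16 | 9.8% | 17% | 42% | 6.5% | 5.8% |
| 24 | 5.9% | 10% | 49% | 4.0% | 2.2% |
| 25 | 5.6% | 7% | 56% | 7.4% | 1.3% |
| 40 | 3.2% | 7% | 56% | 1.6% | 0.3% |

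The tail chances do not fall smoothly, because few shares are possible at each m. At m = 11, for instance, 3 or 8 EG classrooms give 0.24 / (3/11 × 8/11) = 1.21, just over the 20% line, and the chance of crossing it is 33%. The averages are the steadier guide. At m = 24, √1.059 = 1.03, about 3% in width. At 60 units the average increase is 2.1%, and at 100 it is 1.2%.

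**Effect of stratifying.** Holding Mexico near 40:60 brings average relative efficiency from 0.90 to about 1.00 at 10 classrooms, and from 0.83 to about 0.93 at 6.

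**The case against.** The strongest objection is that the premise is not in the document. A reader might infer that Mexico will contribute few classrooms, because the Discussion says that fewer than half of Mexican schools are online. The article does not support that inference. Home access also qualifies, and education authorities in both countries e-mailed all secondary teachers. No count or share is given. This stands, so the point is conditional.

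The cluster count may also be higher than assumed. At 40% EG, 622 in that arm needs 622 / 0.4 = 1,555 participants in all. Registration is individual and voluntary, and families and adults who join by themselves add small units. More and smaller units shrink the loss. If the 60% rule is enforced as an overall quota, the spread of the Mexican split is smaller still: the variance of the EG count falls by (N − m)/(N − 1), which is 40/49 = 0.82 for 10 of 50 classrooms and 56/79 = 0.71 for 24 of 80. Against this, unequal class sizes worsen the split by person. With an assumed coefficient of variation of 0.65, the chance of an EG share under 25% rises to about 22%, 16% and 10% at 10, 15 and 24 classrooms.

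A reader might count every departure from 40% as harm, for example any EG share over 55%. That is wrong. A share of 60% is as precise as 40%, and the harmful upper tail (over 60%) is only about 2–6% at the four assumed counts. In 42–56% of trials at those counts nothing is lost.

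Finally, the article condenses a fuller protocol, and separate national websites exist. Allocation might have been run separately for each country, but the article does not say so, and it presents the two requirements as the constraints on the randomisation.

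**Conclusion.** The point holds as a minor one. The stated allocation rule does not protect balance within country, and the article promises a comparison that depends on it. If Mexico supplies 10–24 classrooms, the expected cost is a 6–17% higher variance for the Mexican effect (3–8% in interval width), with more than 20% in about 10–23% of trials at the counts 10, 15, 16 and 24. If Mexico supplies 25–40, the average is 3–6%; at 40 or more it is about 3% or less.

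These sizes rest on an assumed number of classrooms, equal class sizes and independent allocation at 40% EG. It would be tempting to conclude that the randomisation is unsound or the country comparison biased. The documents do not support that: simple cluster allocation is valid, and country is recorded for adjustment. The loss falls on a contrast that is not a listed aim and for which no power is claimed.

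**What to change.** Add a third requirement in the section on study population and group composition: the computer allocates classrooms or families within country, in concealed permuted blocks of randomly varied size at 3:2 control to experimental (for example blocks of 5 and 10). The first registrant of a classroom or family takes the next place on that country's list. Keep country in the main model as the stratification factor. If allocation was already run separately for each country, say so instead.

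The cost is a small change to the allocation program and no extra participants. Country is known when the arm is assigned, because assignment follows the pre-test that records it. The one drawback is slight predictability at the end of a block, which concealment and varied block sizes limit.

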The statistical analysis will be performed through multivariate regression procedures (using the ‘Enter’ method) to control the effect of potential confounders and modifiers of the effect. Regressions will follow several steps in order to establish the percentage of variability of the result variable which is explained by the remaining variables.

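### The 60:40 allocation to control conflicts with a sample size stated as 622 recruited in each arm with one 20% withdrawal rate

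*Protocol article*

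**What the plan says.** Both statements stand in the protocol article, in the section on study population and composition of the groups.

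- **Allocation.** The first of two conditions on the randomization is that "60% of the users should be assigned to the CG since a higher withdrawal rate is expected in this group". That is 1.5 CG participants for each EG participant, and the only reason given is a higher expected withdrawal rate in the CG.
- **Sample size.** The following paragraph aims to "detect a significant decrease (p<0.05) of at least 10 percentage points in the global behavioral risk indicator" at the post-test and concludes that "it will be necessary to recruit 622 individuals in each arm of the study". It gives 90% power and a withdrawal estimate of 20%.

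The 20% is not divided by arm. The article does not say that 622 is a minimum, gives no total, and does not say how the 60:40 rule entered the calculation. It also gives no SD, baseline level or sidedness for the test.

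**The concern.** The two paragraphs describe different trials. Recruiting 622 in each arm is 50:50; the randomization rule is 60:40. The withdrawal assumptions diverge too: the allocation rule rests on unequal withdrawal, while the sample size carries a single rate.

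What is at stake is the recruitment target and the power attached to it. Someone running the registration system cannot tell whether to stop at a total of 1,244, when the smaller arm reaches 622, or when the larger one does. These readings differ by several hundred participants, and the 90% claim cannot hold equally for all of them.

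**Working it through.** **Inputs from the article:** CG:EG = 60:40; 622 recruited per arm; withdrawal 20%; power 90%; significance level 0.05; a difference of 10 percentage points.

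**Inputs assumed, because the article does not give them:** two-sided test; a comparison of proportions at 50% versus 40%; no clustering; 20% loss in each arm unless stated otherwise.

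**1. Can 622 be reproduced?** Not from the stated inputs alone. Under the assumptions, for equal arms:

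n = [1.960·√(2·0.45·0.55) + 1.282·√(0.4·0.6 + 0.5·0.5)]² / 0.10² = 518.04 per arm.

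- Multiplied by 1.2: 621.6, which rounds up to 622.
- Divided by 0.8: 647.5. This does not match.

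The match does not prove the basis. For example, 44% versus 34% gives about 498 per arm, and 498/0.8 is about 623. Every match found uses equal arms and one common withdrawal rate; none has 60:40 built in.

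**2. What 60:40 does to the arms**

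- Total fixed at 2 × 622 = 1,244: CG 0.6 × 1,244 = 746.4; EG 0.4 × 1,244 = 497.6.
- EG must reach 622: total 622/0.4 = 1,555; CG 933.
- Recruitment stops when the CG reaches 622: EG 622 × 40/60 ≈ 415; total about 1,037.

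**3. Power under each reading**

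Power = Φ[(0.10 − 1.960·s₀)/s₁], where s₀ = √{p̄(1−p̄)(1/n_E + 1/n_C)}, s₁ = √{0.4·0.6/n_E + 0.5·0.5/n_C}, and p̄ is the average proportion weighted by arm size.

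| Reading | Recruited CG / EG | Left after 20% loss, CG / EG | Power |
|---|---|---|---|
| 1:1 as the sample size is worded | 622 / 622 | 498 / 498 | 88.8% |
| 60:40, total 1,244 | 746 / 498 | 597 / 398 | 87.5% |
| 60:40, EG reaches 622 | 933 / 622 | 746 / 498 | 93.6% |
| 60:40, CG stops at 622 | 622 / 415 | 498 / 332 | 81.0% |

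For the second row: p̄ = 0.46, s₀ = 0.03225, s₁ = 0.03196, so Φ(1.151) = 0.875.

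The same formula at 44% versus 34% (0.34·0.66 and 0.44·0.56 in s₁) gives 90.0%, 88.7%, 94.4% and 82.5% in the same order. The pattern does not depend on the assumed baseline.

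**4. How much is due to the split?** At a total of 1,244 and equal loss, 88.8 − 87.5 = 1.3 points. The other 1.2 points below the stated 90% arise because, under the assumed basis, 622 comes from multiplying by 1.2 rather than dividing by 0.8. That is separate from the allocation.

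**5. If CG withdrawal is higher, as the article expects** (total 1,244 at 60:40)

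- EG 10%, CG 26.7% (20% overall): 448 EG and 547 CG remain; power 88.5%.
- EG 10%, CG 40% (28% overall): 448 and 448 remain; power 85.4%.
- EG 20%, CG 40% (32% overall): 398 and 448 remain; power 83.2%.

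**The case against.** The best defence is that 622 is a minimum for each arm. The smaller arm then reaches 622, the larger has 933, and power after 20% loss is 93.6%: nothing is lost. The 20% could likewise be an overall average, with the CG above it and the EG below. Both readings are possible and the text excludes neither. But it states neither, and the first implies a total of 1,555 that appears nowhere. The defence shows that the trial may be adequately sized; it does not make the two statements agree.

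The power effect is also modest on the nearest alternative reading: 1.3 points at a fixed total and equal loss. That stands, and it limits the weight of the point.

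Several stronger readings are tempting but not supported:

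- *The 60:40 split is meant to cure bias from unequal withdrawal, and fails.* The article gives a withdrawal rate as its reason, which concerns numbers. It makes no claim about bias.
- *The trial will be analysed on completers only.* The analysis paragraph describes multivariate regression "to control the effect of potential confounders and modifiers of the effect". It names no analysis population or missing-data method, and an article may leave these to the full plan.
- *The EG necessarily falls short of 622.* This holds if the total is fixed at 1,244 or recruitment stops at 622 controls, not if 622 is a minimum.
- *The split implies particular withdrawal rates in each arm.* That would follow only if 60:40 were meant to give equal numbers of completers, which the article does not say.
- *Controls are denied rewards for the post-test.* The intervention procedure limits their access to website sections. It lists answering the questionnaires among the ways participants earn points and does not exclude controls from this.

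**Conclusion.** The point stands as an internal inconsistency. A 60:40 allocation and 622 recruited in each arm cannot both be exact recruitment targets, and a single 20% withdrawal rate does not reflect the unequal withdrawal used to justify the split. That conclusion needs no assumption.

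The size depends on the reading: a total of about 1,037, 1,244 or 1,555, with power of 81.0%, 87.5% or 93.6%. These power figures rest on an assumed 50% versus 40%, a two-sided 0.05 test, no clustering and 20% loss in each arm. They illustrate the spread and do not reconstruct the sponsor's calculation. They also leave out the clustering that the article's Discussion acknowledges.

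One secondary remark: allocating more people to the CG replaces lost numbers only. It does not protect the comparison if those who leave differ from those who stay, because that depends on who leaves and not on the allocation ratio. The documents give nothing from which to size such an effect.

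**What to change.** Restate the sample size as recruitment targets by arm that follow 60:40, and say which quantity is fixed. Two consistent forms are:

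- CG 933 and EG 622 (total 1,555), if 622 is the minimum for the smaller arm; or
- CG 746 and EG 498 (total 1,244), with the power restated for those numbers.

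In either case, give a withdrawal rate for each arm that matches the expectation of higher CG loss, and state the SD or baseline level and the sidedness behind the figure. Without these, no single corrected number can be derived from the article.

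The cost is rewording and a short recalculation. If the total stays at 1,244, the stated power becomes slightly less favourable. If the EG must reach 622, the cost is 1,555 − 1,244 = 311 more participants.
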